## Abstract

**Background:**

Research has shown that internet-based cognitive behavioural therapy (iCBT) can be a very promising solution to increase access to and the dissemination of evidence-based treatments to all of the population in need. However, iCBT is still underutilized in clinical contexts, such as primary care. In order to achieve the effective implementation of these protocols, more studies in ecological settings are needed. The Unified Protocol (UP) is a transdiagnostic CBT protocol for the treatment of emotional disorders, which includes depression, anxiety and related disorders, that has shown its efficacy across different contexts and populations. An internet-based UP (iUP) programme has recently been developed as an emerging internet-based treatment for emotional disorders. However, the internet-delivered version of the UP (iUP) has not yet been examined empirically. The current project seeks to analyse the effectiveness of the iUP as a treatment for depression, anxiety and related emotional disorders in a primary care public health setting.

**Methods:**

The current study will employ a parallel-group, randomized controlled trial design. Participants will be randomly assigned to (a) the internet-based Unified Protocol (iUP), or (b) enhanced waiting list control (eWLC). Randomization will follow a 2:1 allocation ratio, with sample size calculations suggesting a required sample of 120 (iUP=80; eWLC=40). The Mini-International Neuropsychiatric Interview (M.I.N.I.) will be used for assessing potential participants. The Overall Anxiety Severity and Impairment Scale (OASIS) and the Overall Depression Severity and Impairment Scale (ODSIS) as well as other standardized questionnaires will be used for assessments at baseline, 4 weeks, 8 weeks and 12 weeks from baseline and for the iUP condition during the follow-up.

**Discussion:**

Combining the advantages of a transdiagnostic treatment with an online delivery format may have the potential to significantly lower the burden of emotional disorders in public health primary care setting. Anxiety and depression, often comorbid, are the most prevalent psychological disorders in primary care. Because the iUP allows for the treatment of different disorders and comorbidity, this treatment could represent an adequate choice for patients that demand mental health care in a primary care setting.

**Trial registration:**

ISRCTN18056450 10.1186/ISRCTN18056450.

## Introduction

Epidemiological studies have found that anxiety (e.g. social anxiety, generalized anxiety, panic disorder), anxiety-related disorders (e.g. posttraumatic stress disorder, obsessive-compulsive disorder) and unipolar mood disorders (e.g. depression), sometimes referred to as emotional disorders (ED) [1], account for the highest prevalence of psychological disorders on a global scale [2]. There is a significantly high lifetime prevalence rate for depression, anxiety and anxiety-related disorders coupled with very high comorbidity rates [3]. In Ireland, depression and anxiety are the most common psychological conditions with which patients present to their General Practitioner (GP) [4] and are the most common referrals to primary care mental health settings [5]. These disorders are also associated with enormous costs and disability both directly and indirectly [6]. In relation to treatment methods, research has indicated that psychological treatment is equally as effective as pharmacological [7], and according to McHugh and colleagues [8], clients demonstrated a preference for psychological interventions over pharmacological. Effective evidence-based psychological treatments have been developed and refined; however, many people do not have the resources to access these [9]. The provision of psychological interventions in the context of public health, in some countries like Ireland, is also impacted by the sheer volume of referrals that require the use of extensive wait-lists [10]. In the past 20 years, the emergence of internet-based treatments started to address these gaps in dissemination. This is particularly the case in countries that use low-intensity interventions and a stepped-care approach as part of their public health provision, e.g. [11].

Internet-based cognitive behavioural therapy (iCBT) was developed to improve access to treatment of disorders such as depression or anxiety while maintaining treatment efficacy as well as cost-effectiveness [12]. A growing body of research has shown the efficacy and effectiveness of iCBT for anxiety and depression, e.g. [13–15]. Compared to face-to-face treatments, online treatments offer important advantages not only in terms of dissemination and access to evidence-based treatments, and alleviating personal barriers such as the stigma of physically attending a service, but also by decreasing the workload of mental health care providers with a significant reduction in costs [12].

Research over the past 30 years has provided a myriad of disorder-specific CBT protocols for depression and anxiety [16]. However, although effective, disorder-specific CBT has important shortcomings with regard to dissemination and effective uptake, such as their higher costs (e.g. in terms of training) [17] and less efficiency in addressing comorbid presentations [18]. These reasons, along with the literature showing the role of common mechanisms underlying emotional disorders, shared aetiology and shared comorbidity, have triggered the development and study of transdiagnostic treatments [19, 20]. The Unified Protocol (UP) is a transdiagnostic CBT protocol that addresses the common psychopathological processes underlying emotional disorders, with a particular focus on neuroticism and emotion dysregulation, aspects that play a key role in the onset and maintenance of these disorders [19, 20]. The UP has shown efficacy in a face-to-face format, that it is as effective as well-established disorder-specific CBT [21, 22]. The recent meta-analyses showed its efficacy for depression, anxiety and related conditions [23, 24].

In terms of the number of studies conducted, the UP is a true leader among transdiagnostic interventions [23–25]. However, an internet-delivered version of the UP (iUP) for adults, with the exception of a Spanish UP based programme that also included other elements [26], a German [27] and a Romanian version [28] has not yet been examined. These three previous interventions showed promising results in terms of their outcomes and retention. The three non-English interventions, unlike the current study, were not used in a routine public health primary care setting that is characterized by waiting lists which may require easily disseminated interventions that can reach clients while they are on the wait-list. The current provision in the context of the Irish public health service typically offers minimal self-directed low-intensity interventions. The current study is the first online adaptation of the UP developed by the original developers of the UP and a leading digital mental health company, SilverCloud Health. The current study is also an initial test of the efficacy of the iUP in the context of the setting, primary care, characterized by a high prevalence of (comorbid) depression and anxiety and related disorders.

### Aims of the current research

Our main aim is to test the initial effectiveness of the iUP for depression, anxiety and related emotional disorders against an enhanced wait-list control (eWLC; enhanced in terms that the service routinely offers a number of resources for the clients waiting for an intervention—see below) in the Irish public health primary care service (the Health Service Executive [HSE]). This project aims to answer the following principal research questions:Will the iUP intervention be significantly more effective than the enhanced waiting list control group in treating depression, anxiety and related disorders among the clients in the public primary care?What are the reported experiences (helpful and unhelpful aspects of the treatment and the treatment’s impact) of the clients undergoing iUP as their treatment?

## Method

### Design

The current study will employ a parallel-group, exploratory randomized controlled trial design. The study will follow the CONSORT statement [29], CONSORT E-Health guidelines [30] and the SPIRIT guidelines (Standard Protocol Items: Recommendations for Interventional Trials) [31]. Participants will be randomly assigned to (a) the internet-based Unified Protocol (iUP), or (b) enhanced waiting list control (eWLC). Randomization will follow a 2:1 allocation ratio, with sample size calculations suggesting a required sample of 120 (iUP=80; eWLC=40). Assessments will take place at baseline, 4 weeks, 8 weeks and 12 weeks from baseline. For ethical reasons, the eWLC group participants will be offered iUP treatment after 12 weeks. iUP group participants will be followed up at 16 weeks, 20 weeks and 24 weeks from baseline, so that we can examine (short-term) stability of any effects achieved.

### Participants and study setting

Participants will be adults (18 years old or older) with anxiety and/or depressive symptoms that attend primary care services in Ireland to seek mental health care. To be eligible, participants will have to have a score of ≥ 8 on the Overall Anxiety and Severity Impairment Scale (OASIS) [32] and/or a score of ≥8 on the Overall Depression Severity and Impairment Scale (ODSIS) [33]. The study will take place in a naturalistic setting within a Dublin-based primary care psychology service which is part of the Health Service Executive (HSE) in Ireland. Referrals are made via General Practitioners (GP), allied services, or self-referral. Average wait-list times can range from 3 to 12 months. At the end of the wait-list period, the service usually offers an initial intake assessment followed by an individual care plan, including individual and/or group psychotherapy, delivered by psychologists trained in a variety of therapeutic modalities. The service offers some support for clients on the wait-list (including a lecture series on stress control, a list of self-help books and the possibility to have a 30-min consultation with a psychologist in an advice clinic).

### Sample size

Sample size was determined in relation to the planned analysis of primary outcomes (i.e. linear mixed models of anxiety/depression severity) and calculated in the R package ‘powerlmm’ [34]. Model parameters (random intercept/slope, residual variance) required for this calculation were estimated from similar data from a previous trial on a transdiagnostic intervention in primary care [26]. Given a 2:1 randomization ratio, longitudinal data collected at four timepoints across both groups, 30% research attrition at the primary endpoint and a moderate post-treatment between-group effect size of *d*=0.5 in line with previous research [21, 35], a sample size of 120 (iUP=80, WLC=40) was estimated to yield sufficient statistical power of 0.83 (a Bonferroni-adjusted *p* value of 0.025 to account for two primary outcome measure would reduce power to 0.75; at a lower attrition rate of 20% rather than 30%, power of 0.80 would be reached even with the Bonferroni-adjusted *p* value).

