### Data analysis

All the analyses will follow the intention-to-treat principle and reporting of the results will adhere to CONSORT recommendations. Missing data analysis will explore missing data patterns and mechanisms. Multiple imputation will be considered where deemed necessary. Linear mixed models will be used to evaluate primary and secondary outcomes. In these models, intercepts and/or slopes will be allowed to vary on the level of the individual where appropriate and time and treatment group as well as their interaction will be included as fixed effects. To allow for the nesting and comparing of models in terms of model fit, models will be estimated via maximum likelihood estimation during model building. Final models will utilize restricted maximum likelihood estimation. Separate linear mixed models utilizing only data from the iUP group will be built to assess the maintenance of effects into follow-up, including random intercepts/slopes and time as a fixed effect. Between-group Cohen’s *d* effect sizes will be calculated based on raw standard deviations [52]. The qualitative data will be analysed using a descriptive-interpretive approach [53].

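### The sample of 120 is justified by a power of 0.83 at an unadjusted 0.05 for each of two primary outcomes, with no commitment to a multiplicity adjustment or success rule

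*Protocol article*

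**What the plan says.** The Measures section of the protocol article lists OASIS and ODSIS as primary outcomes and ranks neither above the other.

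The Sample size section ties the calculation to both: "Sample size was determined in relation to the planned analysis of primary outcomes". With 2:1 allocation, four timepoints, 30% attrition and a "moderate post-treatment between-group effect size of *d*=0.5", the sample of 120 "was estimated to yield sufficient statistical power of 0.83". A bracket then adds that a Bonferroni-adjusted "value of 0.025 to account for two primary outcome measure would reduce power to 0.75", and that "at a lower attrition rate of 20% rather than 30%, power of 0.80 would be reached even with the Bonferroni-adjusted" level. The unadjusted significance level and the sidedness are not stated.

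The Data analysis section says "Linear mixed models will be used to evaluate primary and secondary outcomes". It gives no significance level, no multiplicity rule and no rule on whether one or both primary outcomes must succeed. The Design section calls the trial exploratory. The Aims section asks, as a principal question, whether iUP is significantly more effective than the enhanced waiting list.

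**The concern.** The protocol recognises that two primary outcomes call for a stricter test, gives the cost in power, and leaves the matter open. The figure called sufficient belongs to the unadjusted level. The reassurance that 0.80 survives the adjustment depends on 20% attrition, whereas the plan itself assumes 30%.

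Two things are at stake. The reader is given a headline power that the adjusted test does not have under the plan's own assumptions. And a positive trial is not defined in the visible text: a significant result on one scale alone could be read as success or as failure, and that choice could be made after the results are known.

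**Working it through.** **Inputs from the Sample size section:** power 0.83 at 30% attrition; 0.75 at a level of 0.025; 0.80 at 0.025 with 20% attrition; two primary outcomes; N = 120.

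**Assumptions:** two-sided tests; the same noncentrality for both outcomes; correlation between the two test statistics from 0 to 0.9, because the document gives none.

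**1. Level behind 0.83.** The implied noncentrality at two-sided 0.05 is 1.960 + 0.954 = 2.914. At 0.025 the critical value is 2.241, so power = Φ(2.914 − 2.241) = Φ(0.673) = 0.749, against the stated 0.75. Starting from 0.10 instead, the noncentrality is 2.599 and power at 0.025 would be 0.640. So 0.05 is the level that fits.

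**2. The 20% attrition figure.** Scaling the noncentrality by √(0.8/0.7) = 1.069 gives 3.115. Power at 0.025 = Φ(3.115 − 2.241) = Φ(0.874) = 0.809, against the stated 0.80. The scaling is approximate, since a mixed model also uses partial data from dropouts.

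**3. What each possible rule delivers at N = 120 and 30% attrition** (bivariate normal, noncentrality 2.914 on both outcomes for the power columns, zero for the error column). Under Holm an outcome is rejected if it passes 0.025, or if it passes 0.05 while the other passes 0.025.

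| Correlation | Either at 0.05: family-wise error | Both at 0.05: joint power | Holm: power per outcome |
|---|---|---|---|
| 0 | 0.0975 | 0.689 | 0.810 |
| 0.5 | 0.091 | 0.729 | 0.800 |
| 0.7 | 0.083 | 0.752 | 0.794 |
| 0.9 | 0.070 | 0.785 | 0.786 |

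At correlation 0 the error is 1 − 0.95² = 0.0975. Plain Bonferroni gives 0.749 per outcome whatever the correlation, and 0.94 to 0.81 for at least one success (correlation 0 to 0.9). None of the rules that control the error has a per-outcome or joint power of 0.83.

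**4. Limit of the check.** The absolute 0.83 cannot be rebuilt, because "Model parameters (random intercept/slope, residual variance) required for this calculation were estimated from similar data from a previous trial" and their values are not given. Under one assumed set (intraclass correlation 0.7, slope-to-residual variance ratio 0.02, d on the baseline standard deviation) an analytic mixed model gives 0.836, 0.756 and 0.800. The three stated figures are therefore compatible with one another, and the absolute 0.83 is not disputed here.

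**The case against.** A reader might infer that the trial will test both outcomes at an unadjusted 0.05, that a win on either suffices, and hence that 0.83 is bought with a false-positive rate of 8-10%. The document does not support this. No section states the test level or an either-outcome rule. The principal question can also be read as requiring both outcomes, in which case there is no family-wise inflation. The 8-10% range also needs a correlation of no more than about 0.75; at 0.9 the error is 7.0%.

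Three further objections carry weight. The 0.75 is disclosed in the same sentence as the 0.83, so nothing is hidden. The trial is labelled exploratory. And a multiplicity procedure is commonly set out in an analysis plan, which is not shown here, so its absence from a journal article is not in itself a fault.

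These points lower the severity but do not remove the point. It concerns what the Sample size section does state: it calls sufficient a power computed at the unadjusted level, while giving a lower figure for the adjusted one. If an unseen plan adopts Bonferroni or Holm, 0.83 is not the power of the planned test. If it requires both outcomes, the relevant power is lower still. If it adopts nothing and lets either outcome count, the error rate exceeds 5%. The sentence needs rewording in each case. The exploratory label also sits beside a principal question framed as a significance test and a formal power calculation.

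**Conclusion.** The point holds, at moderate severity. The sample of 120 is justified at an unadjusted two-sided 0.05 for each of two primary outcomes, and the visible text commits to no adjustment or success rule. At the protocol's own Bonferroni level and planned attrition, power per outcome is 0.75, which is 0.08 below the headline; 0.80 is reached only at 20% attrition. Depending on the rule eventually used, the consequence is a family-wise error of about 7-10% (either outcome at 0.05) or a joint power of about 0.69-0.78 (both required at 0.05). These ranges rest on an assumed correlation of 0.9 to 0, and the joint power also on an equal effect on both scales. The 0.05 level and two-sidedness are inferred from the step from 0.83 to 0.75.

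It would be wrong to conclude that the sample is too small. Under Holm, power per outcome stays at about 0.79-0.81 if d = 0.5 holds for both outcomes.

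**What to change.** State in the Sample size and Data analysis sections that OASIS and ODSIS are tested with the Holm procedure at a family-wise two-sided alpha of 0.05, and that iUP is declared effective on each outcome rejected. Replace the 0.83 headline with the controlled figure at 30% attrition: at least 0.75 per outcome (the Bonferroni bound), and about 0.79-0.81 under Holm if both outcomes have d = 0.5 (correlation 0.9 to 0, assumed). The 0.75 should be described as a lower bound, not as Holm's power. If an analysis plan already fixes a different rule, the Sample size section should quote the power of that rule instead.

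The cost is a few sentences and a slightly lower stated power per outcome (from 0.83 to about 0.79-0.81, or 0.75 as the bound). No more patients are needed. The change should be made before outcome data are seen by group.

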#### Intervention

##### Internet-based Unified Protocol (iUP)

The iUP is an eight-module online intervention that is based on the second edition of the UP [21, 36]. It includes the five core CBT modules in the UP that target neuroticism (i.e. negative affect and aversive reactivity to emotions) and subsequent emotion motivated avoidant coping [37]. See Table 1 for an overview of the modules. The programme is self-directed, so the client can proceed through the programme at their own pace. The recommended time to spend on a module is initially 1 week, but starting with module 3, and for the rest of the core modules in the UP (Table 1), the supporter (see below) may suggest extra time, 2 or more weeks. Supporters particularly recommend that participants spend 2–4 weeks on module 7 (Emotion Exposures). Specific recommendations from supporters will also consider participant pace, progress and engagement with the programme (e.g. if someone does not complete a specific module 1 week, they may be encouraged to complete it the following week). This intervention will be delivered on the SilverCloud platform. SilverCloud Health is a global leader in the development of computerized psychological interventions for depression, anxiety, stress and comorbid long-term conditions. The intervention will be delivered on a Web 2.0 platform using media-rich interactive content. Consistent with other SilverCloud programmes, each module follows a structured format and includes videos, a psychoeducational content, interactive activities and tools, instructions for practicing skills and summaries of the modules. Clients’ progress and use of the iUP will be reviewed by a supporter, who will provide feedback on the client’s use of the programme. Their support will consist of email messages to the clients that provide encouragement and suggestions for the use of the programme. The feedback will be provided every 6 to 10 days. The supporters will be assistant psychologists and/or trainee psychologists. They will be under supervision of a qualified psychologist. All participating clinicians will be trained by an UP trainer in the delivery of support for iUP and in addition will receive training on the platform and how to deliver supporter reviews to participants.

**Table 1 Tab1:** Modules in the Internet-based UP

Module name	Brief description
Getting Started	This module introduces the UP and how it can be helpful in managing emotions. Additional content focuses on goal setting and motivation. Users set specific goals and consider the pros and cons of changing.
Understanding Your Emotions	This module provides psychoeducation about the nature and function of emotions. Users learn that all emotions can be broken down into 3 components: thoughts, physical sensations and behaviours, that each interact with the others. Antecedents or triggers of emotions are identified, as well as short- and long-term consequences of responses to emotions.
Mindful Emotion Awareness^a^	This module introduces mindful emotion awareness as a skill to use in response to emotion. The two components are present-focused awareness and non-judgmental awareness. Several ways to practice this skill are covered including a guided meditation exercise, practicing while watching an emotional video clip, and applying the skill in daily life.
Flexible Thinking^a^	This module focuses on thoughts and their connection to emotions. Users learn how to identify negative thinking patterns and develop skills to practice thinking more flexibly.
Emotional Behaviours^a^	This module focuses on the behavioural component of emotions. Users learn how identify emotional behaviours (behaviours to avoid or decrease emotions) and how to practice changing their behaviour through alternative actions.
Facing Physical Sensations^a^	This module focuses on the physical sensations component of emotions. Users learn about the importance of context and their interpretation of physical sensations, and complete interoceptive exposures exercises to physical sensations (e.g. hyperventilation, straw breathing, spinning and running in place).
Emotion Exposures^a^	This module focuses on emotion exposures, activities, or situations designed to intentionally bring up strong emotions. Users create a hierarchy of exposures, and learn how to practice applying all of the skills they have already learned in the programme while preparing for, engaging in, and debriefing from exposures.
Progress and Practice	This final module focuses on reviewing progress, relapse prevention, and making a plan to continue practicing skills after the programme.

^a^ indicates core modules in the UP

